**Methods:**

In a mixed-method study incorporating a quantitative survey and qualitative instruments, we investigate the prevalence of violence, including both victimization and perpetration, among people with SMI. Our study includes the following: (1) In a sample (n=500) of people with SMI, treated in inpatient and outpatient mental health settings, we will investigate the prevalence of victimization and violent behavior, (self-)stigmatization, and barriers for disclosure of experiences of violence within mental health settings. Data will be obtained from samples at seven psychiatric hospitals with mandatory care on a fixed day. For comparisons with the general population, we use an online sample (n=1000). (2) Based on this, we conduct qualitative interviews with a subsample of people with SMI (n=30) who reported experiences of violence. Using biographic-narrative interviews, we focus on the biographical and socio-cultural context (3). In addition, we use qualitative and quantitative measures to investigate mental health professionals’ experiences, institutional factors, and strategies to deal with mental health service users’ violence experiences.

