### Study design

We conduct a cross-sectional mixed-method study consisting of three subprojects. The mixed-method-design will be realized by combining quantitative survey data (subproject 1) and subsequent qualitative narrative-biographical interviews (subproject 2) in line with an Explanatory Sequential Design (34). Qualitative focus groups, interviews and subsequent survey data (subproject 3) will be combined according to the Exploratory Sequential Design (34).

Subproject 1: Quantitative cross-sectional survey with mental health service users.We will conduct a quantitative cross-sectional study involving 500 people with SMI through a key date survey conducted in various psychiatric clinics. Additionally, a representative sample of 1000 individuals from the general population will be surveyed by USUMA, a German market and social research institute.Subproject 2: Qualitative study with mental health service users.

We will conduct a qualitative study using narrative-biographical interviews data involving a subsample of approximately 30–40 people with SMI from subproject 1.

Subproject 3: Qualitative study and quantitative survey with mental health professionals.

In a first step, we will collect qualitative data through approximately 30 semi-structured interviews and four focus groups with mental health professionals. In a second step, we collect quantitative data from approximately 100 mental health professionals.

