### Participant timeline

The recruitment period for participants in subproject 1 has started in January 2024 and will continue until August 2025. At the time of submitting this protocol, 250 participants have been included in the study. The recruitment of participants for the narrative-biographical interviews in subproject 2 has started in August 2024, with the interviews set to be conducted until August 2025. Participants for the qualitative interviews in subproject 3 have been recruited since March 2024, with the recruitment period scheduled to end in February 2025. At the time of the submission of this protocol, (n=29) interviews have been conducted. Participants for the focus groups in subproject 3 are scheduled to begin in December 2024 and will be conducted until June 2025. Participants for the questionnaire survey in subproject 3 will be included in the study from October to December 2025.

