### Recruitment and sample size calculation

#### Subproject 1 (quantitative cross-sectional survey with mental health service users)

Focusing on people in psychiatric treatment allows us to survey a representative sample of a defined population. This group represents those with immediate access to therapeutic interventions, and therefore to potentially address experiences of violence. A sufficiently large sample is targeted to enable adequate analyses of different context factors. The sample size of n=500 is chosen to enable the most precise estimation possible of the prevalence of violence experiences.

For statistical power analysis regarding the sample size in subproject one, considering the overall exploratory nature of this study, the variety and theoretical parity of the variables of interest (no primary predictor), and the scarcity of published data that could guide a strict *a priori* power analysis, we liberally set the sample size to 500 or 100 per clinic, respectively. This sample size is sufficient to detect group differences of medium to large effect sizes with a maximum error rate of 5% for both Type I (alpha) and Type II (beta) errors. We illustrate this with the analysis of clinic-level effects using G*Power 3.1.9.7 (36). Based on 500 data points, global parametric comparisons for independent groups can detect site effects on metric variables such as respondent’s age down to f=0.20 with a power of at least 95% (one-way ANOVA with fixed effects, 5 equally-sized groups). This corresponds to site effects on ordinal (e.g. socioeconomic status), nominal (e.g. marital status), or binary variables (e.g. gender) of w≥0.20 (Chi^2^-distribution based tests, df=4). For comparison, a previous study by Johnson et al. (2015) (37) found only a marginal effect of gender on participant status as victim, perpetrator or victim/perpetrator compared to people who did not experience violence (w=0.06, p<0.01). However, comparability of this study’s sample with our target population is strongly limited, as men and people with schizophrenia were overrepresented (59.8% and 63.4%, respectively). For our study, we expect considerably more women than men in psychotherapeutic services (38) and lower rates of schizophrenia, given a prevalence rate of less than 1% in Germany (27).

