Participants will be recruited at the following cooperating hospitals: Clinic and Polyclinic for Psychiatry and Psychotherapy, University Hospital of Leipzig (urban area) (n=100); “Helios Park” - Hospital Leipzig (urban area) (n=100); District Hospital Guenzburg (small town/rural area) (n=100); Specialized Hospital Bethanien Hochweitzschen (rural area) (n=100); Helios Hanseatic Hospital Stralsund (rural area) (n=100). Since violence is a taboo topic, we expect that many people may not want to participate in our study. In order to still obtain a sufficiently large sample size to calculate the aforementioned statistical parameters, we have additionally collaborated with the following two clinics: The Clinic for Psychosomatic Medicine and Psychotherapy at the University Hospital Ulm (urban area). Further, we cooperate with the Clinic for Psychiatry, Psychotherapy and Psychosomatics, Saxon Hospital Altscherbitz, Germany (outskirt of Leipzig). A cooperation has been requested with the Clinic for Psychiatry and Psychosomatics at the District Hospital and the University of Augsburg (urban area).

On a specified key date, the project staff will approach all patients who are receiving partial or full inpatient treatment. For practical reasons, different key dates will be chosen for various treatment units (wards, outpatient clinics). Recruitment will continue in each clinic until the target sample size is reached. Inclusion criteria were legal age (18 years) and German language skills. Exclusion criteria were dementia, intellectual impairment, current psychotic symptoms, and if the person was in isolation or fixation. All patients that meet the inclusion criteria and don’t need to be excluded for above mentioned reasons will be asked if they would agree to fill out the questionnaire. They will be handed the participants information and fill out informed consent (see section “Ethics”).

Furthermore, we will recruit a general population sample (n=1000) through an online survey conducted by USUMA.

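### Stopping each clinic at its target, with key dates that differ by unit, can let visiting order set the unit mix, so the fixed-day and representative-sample statements are not secured

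*Protocol article*

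**What the plan says.** The article describes the sampling of patients in subproject 1 in four places.

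- **Abstract, Methods:** "Data will be obtained from samples at seven psychiatric hospitals with mandatory care on a fixed day".
- **Study design:** the 500 patients are reached "through a key date survey conducted in various psychiatric clinics".
- **Recruitment and sample size calculation, Subproject 1:**
  - On the aim: "Focusing on people in psychiatric treatment allows us to survey a representative sample of a defined population".
  - On the number: "we liberally set the sample size to 500 or 100 per clinic, respectively".
  - On the procedure: "On a specified key date, the project staff will approach all patients who are receiving partial or full inpatient treatment". Two qualifications follow: "For practical reasons, different key dates will be chosen for various treatment units (wards, outpatient clinics"; and "Recruitment will continue in each clinic until the target sample size is reached".
- **Participant timeline:** "The recruitment period for participants in subproject 1 has started in January 2024 and will continue until August 2025".

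The target of 100 is listed for five hospitals. Two further clinics were added because refusals were expected, and no target is given for them. The section justifies 500 by the precision of the prevalence estimate, and the Outcomes section makes the frequency of violence the primary outcome of subproject 1.

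**The concern.** A key-date approach ends when everyone present has been approached. A quota ends at a number. The recruitment section adopts both and does not say which governs when they disagree.

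They can disagree in two ways. A clinic may reach 100 before all its units have had their date, and the remaining units then contribute nobody. Or a full round may fall short of 100, recruitment goes on, and the target is met part-way through the next round, so the units visited first are over-represented. Either way the unit mix follows the order of visits and not the clinic's patient population. Full non-refusal would not cure this.

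Violence experience may well differ between, say, acute, addiction, open and day units; the protocol itself treats psychopathology as a correlate. A unit mix that depends on order can therefore shift the prevalence that the 500 patients are meant to estimate, and the final sample size would not reveal it.

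**Working it through.** **1. The plan's own figure.** The only power figure is for site effects: N = 500, five equal groups, alpha 0.05, power at least 95% at f = 0.20 or w = 0.20.

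- ANOVA: noncentral F, df 4 and 495, λ = N·f² = 500 × 0.04 = 20, power 96.2%.
- Chi-square: df 4, λ = N·w² = 20, power 96.4%.

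The figure is reproduced, and this point does not touch it. It says nothing about unit coverage.

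**2. The statements set against the rule.** The abstract speaks of a fixed day. The recruitment section gives each unit its own date, and the timeline runs from January 2024 to August 2025, which is 12 + 8 = 20 months. The claim of representativeness needs every unit of a clinic to contribute roughly in proportion to its patients. The stop rule does not secure that, because it does not require a complete round.

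**3. Size of the bias within a clinic.** Take two groups of units, A and B, with prevalences p_A and p_B. Let c be the share of A among the clinic's patients and s its share in the sample. Then

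bias = (s − c) × (p_A − p_B).

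If B is never visited, s = 1 and 1 − c = u is the unvisited share, so the absolute bias is u × d with d = |p_A − p_B|. The documents give neither u nor d. Assumed ranges:

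| Unvisited share u | d = 5 points | d = 10 points | d = 20 points |
|---|---|---|---|
| 10% | 0.5 | 1.0 | 2.0 |
| 20% | 1.0 | 2.0 | 4.0 |
| 30% | 1.5 | 3.0 | 6.0 |
| 50% | 2.5 | 5.0 | 10.0 |

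**4. From clinic to pooled estimate.** With five clinics of 100, the pooled bias is the mean of the five clinic biases. If one clinic is affected, the range of 0.5 to 10 points becomes 0.1 to 2.0 points (divide by 5). Only if all clinics are affected alike does the within-clinic figure carry over unchanged.

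**5. Against sampling error.** The 95% half-width is 1.96 × √(p(1 − p)/n).

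- n = 500: 3.5 points at p = 0.2 and 4.4 points at p = 0.5.
- n = 100, p = 0.21: 1.96 × √(0.21 × 0.79/100) = 8.0 points.

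**6. One worked case, all inputs assumed.** 60% of patients are in units with 15% prevalence and 40% in units with 30%. The census value is 0.6 × 0.15 + 0.4 × 0.30 = 21.0%. If the sample fills 85:15, it is 0.85 × 0.15 + 0.15 × 0.30 = 17.25%, a bias of −3.75 points. For that clinic this is less than half of its 8.0-point half-width. Pooled with four unaffected clinics it is 3.75/5 = 0.75 points. It exceeds the pooled half-width of 1.96 × √(0.21 × 0.79/500) = 3.6 points only if all five clinics are skewed equally and in the same direction.

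**7. Repeat entry, for completeness.** If a share r of the 500 records are second questionnaires and repeaters differ by d, the bias is r × d. Assumed r of 2–10% and d of 10–20 points give 0.2 to 2 points. At r = 5% and d = 20 points it is 1 point, with 475 distinct persons and ANOVA power of 95.3%.

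**The case against.** The strongest reply is that early filling looks unlikely. The recruitment section expects many refusals, two clinics were added for that reason, and a third was requested. The timeline reports 250 included at submission: 250/5 = 50 per clinic over five clinics, or 250/7 ≈ 36 over seven. That points to clinics falling short, not filling early. The text also says all patients will be approached, and nowhere says that the stop rule overrides this. This stands as far as it goes: a reader might infer that some units are in fact left out, and the documents do not show that. But averages do not exclude early filling in a single clinic. A shortfall also leads to the other case, a further round that may end part-way. That a further round means returning to the same units is itself an inference from recruitment continuing; it is not stated.

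Second, the abstract promises samples, not a census, and the recruitment section openly says that dates differ for practical reasons. That is fair. The mismatch with the fixed day is one of description; the weight rests on the stop rule and the claim of representativeness.

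Third, a reader might infer that patients who change unit or are readmitted are counted twice. The documents do not support that as a finding. No once-per-person rule is stated, but a condensed article may leave it to the full protocol. The design speaks of 500 people, consent is signed, and a cipher links records to persons. The Confidentiality section gives the cipher's use only as deletion on withdrawal, yet it could serve to detect repeats.

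Fourth, a reader might take the bias to exceed the sampling error of the headline prevalence. The worked case shows that this needs all clinics skewed alike on assumed inputs.

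**Conclusion.** The point holds in a conditional form. As written, the rule permits a clinic to close with its units unevenly covered, and it therefore does not secure the representative sample or the fixed day that the article claims. Whether this happens depends on unit sizes, response and visiting order, none of which the documents give.

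The within-clinic bias is about 0.5 to 10 points under the assumed shares and differences. It is one fifth of that in the pooled estimate if one of five equal clinics is affected. It can match or exceed the pooled sampling error of 3.5 to 4.4 points, but only if the skew is large and shared across clinics. The stated power is unaffected. The stop rule also has no number to work with at the two added clinics.

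The change is worth making because it corrects a stated rule at little cost. Repeat entry is a matter for clarification only.

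**What to change.** In the recruitment section for subproject 1, replace the stop rule with: *A clinic closes only after a complete round of all its units; any further round again covers all units.* If a clinic must be held at 100, split the 100 over its units in proportion to their census before starting. State which rule applies at the two added clinics.

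Record, for each clinic, the units visited and the numbers approached and consenting per unit, and report them. Describe the sample, in the abstract too, as staggered unit key dates over January 2024 to August 2025. If full rounds were not achieved, do not call the sample representative.

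As a clarification, state that each person is included once, checked against the consent and cipher records of participants. Barring people who declined earlier is a different matter: the documents describe no list of them, so it is not proposed here.

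The cost is a slight overshoot of 100 or some quota planning, a unit log, and a wording change through the amendment route the article already describes. Clinics already sampled can be reported by unit only if such records were kept, which the article does not say.

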
According to Thom et al. (27) around 37.9% of the population are affected by a mental illness. Recent reviews emphasize that despite evidence of elevated victimization rates among people with SMI, representative prevalence studies that allow for cross-country comparisons and population-based estimates in Germany remain scarce (28). Moreover, more research is needed to provide a comprehensive picture of the risk variables influencing victimization experiences (29). Taken together, these gaps highlight the need for further research that combines representative prevalence data with an analysis of social, biographical and institutional factors to provide a more comprehensive understanding of victimization among people with SMI.

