### Outcomes

#### Subproject 1 (quantitative cross-sectional survey with mental health service users)

The primary outcome of subproject 1 is the frequency of violence experiences among people with SMI, both as victims and perpetrators, compared to a control group from the general population. The study examines correlates and contextual factors of violence, such as gender, socioeconomic status, social support, coping resources, and psychopathology. The secondary outcomes include the impact of internalized stigmatizing beliefs among people with SMI, especially in relation to violence experiences. Furthermore, barriers of disclosure will be assessed, focusing in whom these experiences have been communicated to, why or why not, and whether they have been incorporated into treatment if reported in a clinical setting.

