The rationale for including a comparison group from the general population is to contextualize prevalence estimates observed among people with SMI and to determine whether observed rates exceed background population levels. The general population sample is recruited via an online survey conducted by USUMA, which enables access to a large and heterogeneous sample and allows quota sampling based on key sociodemographic characteristics (e.g., age, gender, and region), thereby supporting structural comparability between groups.

People with SMI are recruited in psychiatric services and complete the same standardized self-report measures on-site (paper-pencil or tablet-based). Although both samples rely on identical instruments, differences in recruitment context and survey mode (online vs. clinical setting) may introduce potential mode effects, which will be considered as a potential limitation when interpreting group differences in prevalence.

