### Data analysis

#### Statistical methods

For subproject 1 and subproject 3, we will describe the type, frequency and context of experienced and exerted violence and compare groups by t-test and ANOVAs. Associations will be analyzed by regression and correlation models (60). Further, we consider multilevel models to analyze group-specific association of varying variables with experienced and exerted violence (61, 62). To assess the psychometric characteristics of new developed and translated questionnaires, descriptive analyses and factor analysis will be conducted (60). Finally, we will interpret the qualitative and quantitative data in conjunction and present the results integratively using joint displays (34, 63).

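### Quotas do not align the online sample with the clinic sample, and no adjustment for sex, age or region is tied to the primary comparison

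*Protocol article*

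**What the plan says.** All references are to the protocol article.

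- **Outcomes, Subproject 1:** the primary outcome "is the frequency of violence experiences among people with SMI, both as victims and perpetrators, compared to a control group from the general population".
- **Study design:** the 1000 online respondents are described as a representative general-population sample.
- **Recruitment and sample size calculation, Subproject 1 (comparison group):** the online survey "allows quota sampling based on key sociodemographic characteristics (e.g., age, gender, and region), thereby supporting structural comparability between groups". The limitation named for this comparison is the difference in recruitment context and survey mode.
- **Same section (clinics):** every eligible patient present on a key date is approached. Five hospitals have targets of 100 each (two urban, one small-town/rural, two rural), and two further clinics were added. No sociodemographic quotas are set.
- **Same section (sample size):** "we expect considerably more women than men in psychotherapeutic services". No share is given.
- **Statistical methods:** "we will describe the type, frequency and context of experienced and exerted violence and compare groups by t-test and ANOVAs". The next sentence reads "Associations will be analyzed by regression and correlation models". Multilevel models are under consideration for group-specific associations.

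**The concern.** Quotas on age, gender and region bring a sample closer to whatever distribution they are set to. For a sample meant to represent the population, that is the population distribution. They do nothing to bring it closer to patients found on key dates at particular hospitals. The article expects a female excess in its clinical setting and, in the same section, relies on a quota on gender as support for comparability.

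This would matter less if the analysis dealt with the imbalance. But the only tool named for comparing groups is the t-test or ANOVA, with no covariates, and the regression sentence is not linked to the SMI versus population contrast. If that contrast is reported crude, any variable that differs between the samples and is related to violence becomes part of the difference. Sex is the clearest candidate. The Introduction reports higher sexual victimisation in women than in men with SMI, with a wider gap in the general population. For physical violence it reports similar rates by sex in SMI and typically higher rates in men in the population.

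**Working it through.** **The article's own figure.** With 500 patients, five equal clinics and alpha 0.05, the noncentrality is 500 × 0.20² = 20. Power is 96.2% for f = 0.20 (noncentral F, 4 and 495 df) and 96.4% for w = 0.20 (noncentral chi-square, 4 df). The stated power of at least 95% is reproduced. It concerns differences between clinics, not the comparison with the population.

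**Size of a sex-composition artefact.** Inputs from the article: 500 patients and 1000 online respondents. Assumed, because the article gives no figures: the outcome is yes/no; sex-specific rates are identical in both groups, so the true SMI difference is zero; women make up 50% or 51% of the online sample and 60 to 70% of the clinic sample.

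Crude difference = (share of women in clinics − share online) × (rate in women − rate in men).

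The test is a pooled two-proportion z-test, two-sided at 5%. It stands in for a t-test on a yes/no outcome.

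Worked case with rates of 40% in women and 10% in men, 60% women in clinics and 51% online:

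- Clinic prevalence: 0.60 × 0.40 + 0.40 × 0.10 = 0.280
- Online prevalence: 0.51 × 0.40 + 0.49 × 0.10 = 0.253
- Difference: 0.09 × 0.30 = 0.027
- Pooled prevalence: (140 + 253)/1500 = 0.262
- Standard error: √(0.262 × 0.738 × (1/500 + 1/1000)) = 0.0241
- z = 0.027/0.0241 = 1.12, giving a rejection probability of about 20%

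Each range below runs from 60% to 70% women in the clinics.

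| Rate in women / men (assumed) | Women online | Crude difference (points) | Odds ratio | Rejection (nominal 5%) |
|---|---|---|---|---|
| 40% / 10% | 51% | +2.7 to +5.7 | 1.15 to 1.33 | 20 to 65% |
| 30% / 6% | 50% | +2.4 to +4.8 | 1.17 to 1.35 | 20 to 60% |
| 10% / 2% | 51% | +0.7 to +1.5 | 1.13 to 1.27 | 8 to 20% |
| 12% / 15% | 51% | −0.3 to −0.6 | 0.98 to 0.95 | 5 to 6% |
| 20% / 30% | 51% | −0.9 to −1.9 | 0.95 to 0.90 | 7 to 13% |

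In every row a sex-specific or sex-adjusted estimate would be zero.

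**Scale.** With 500 against 1000, the difference detectable with 95% power is about 8.5 points at a population prevalence of 20% and 9.4 points at 30%. The largest artefact, 5.7 points at a population prevalence of 25.3%, is below these but is about 60 to 67% of them (5.7/9.4 = 0.61; 5.7/8.5 = 0.67).

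**Age and region.** No calculation is possible. The article states no expected age imbalance. For region it shows only that the clinics are a few named sites in urban, small-town and rural areas.

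**The case against.** The strongest reply is that the article does not commit to a crude primary contrast. The t-test and ANOVA sentence is generic and covers Subprojects 1 and 3. Regression follows it, gender and socioeconomic status are listed among the correlates to be examined, and gender is a core aim. This stands: a reader might infer that the comparison is fixed as unadjusted, but the text leaves adjustment open. It simply does not assign it to this contrast.

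A second reply is that covariate lists belong in a full protocol or analysis plan that is not shown. That is fair for model details. It does not rescue the comparability sentence, which is the article's own reasoning and does not follow from the design described. The sentence claims only support for comparability, and it does not say which distribution the quotas target. If they were set to the clinic mix, the inference would hold, but the online sample would then no longer be representative of the population, as Study design says it is.

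Third, the Introduction cites 5-fold odds for physical violence and almost ten times the risk of sexual violence in women. Against effects of that order, an odds ratio of about 1.1 to 1.35 would shift an estimate rather than overturn it. This also stands. The rejection rates above apply to a true difference of zero.

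A reader might also object that the comparator is contaminated, since "around 37.9% of the population are affected by a mental illness". The documents do not support that as a defect. The declared purpose is to see whether rates exceed background population levels, and the background includes people with mental illness. The 37.9% is also any mental illness, not SMI.

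**Conclusion.** The point holds in a limited form. The statement that quotas support structural comparability between the groups is not justified by the sampling described, and no adjustment, weighting or standardisation is tied to the primary contrast. A crude comparison may therefore mix an SMI difference with sex composition, and possibly with age and region.

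From sex alone, under the assumed inputs, the artefact is about +2 to +6 points where rates carry a large female excess, as may be the case for sexual violence. It is smaller where rates are low, near zero where they are similar, and about −1 to −2 points in the example with higher rates in men. It could thus inflate one outcome and mask another. Size and direction rest on assumed rates and shares of women, not on figures in the article.

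A reader might go further and conclude that demographic differences are bound to be reported as an SMI effect. The article does not say so, and the regression it plans could prevent it.

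**What to change.** 1. **Comparison-group text:** say that quotas make the online sample resemble the general population, and that demographic imbalance with the clinic sample remains. Name this as a limitation beside survey mode.
2. **Statistical methods:** state that the SMI versus population contrast will be estimated with a binary-outcome model (logistic or modified Poisson) adjusted for sex and age, or standardised to the SMI sample's sex and age mix, and for region or urbanicity where available. Report sex-specific results and the crude prevalences alongside. The sex-specific results matter in their own right, because the Introduction leads one to expect a different gender gap in the two groups.

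Optional additions are a sensitivity analysis using the social desirability scale already in the questionnaire, and a secondary contrast with online respondents who report no psychiatric treatment.

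The cost is a few sentences, a little more analysis and slightly wider intervals. Age and gender are in the questionnaire, both samples use identical instruments, and clinic locations are known, so no new recruitment is needed.
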